## Abstract

(1) *Shigella* spp. (Shigella) is known for causing dysentery with blood in stool, but most children infected with Shigella have non-dysentery Shigella-associated diarrhea (NDSD). The World Health Organization recommends the use of antibiotics when diarrhea is bloody, leaving most NDSD cases untreated. The absence of dysentery may not indicate a low risk of death and severe morbidity. Rapid diagnosis and treatment of shigellosis in vulnerable, young children may be lifesaving. INSIGHT aims to determine the potential benefit of identifying NDSD cases (n = 296) and their outcomes compared to cases of *Shigella dysentery* [DS (n = 148)] and non-Shigella watery diarrhea [WD (n = 148)]. (2) Children seeking care at hospitals in Bangladesh will be enrolled and followed for 1 year (NDSD and DS) or 90 days (WD). We will determine the impact of NDSD on morbidity, mortality, gut health, nutritional status, and cognitive development compared to DS and WD in children and whether the simple “Rapid LAMP-based Diagnostic Test (RLDT)” can accelerate the detection and treatment of shigellosis in the clinical settings of rural Bangladesh. (3) INSIGHT will determine the impact of NDSD in children and determine if the treatment guidelines of shigellosis need to be revisited to improve clinical outcomes and the development of these children.

## 1. Introduction

*Shigella* spp. (Shigella) is a bacterial pathogen that is frequently associated with diarrheal disease and is a significant cause of mortality and morbidity worldwide. Although the mortality associated with shigellosis has decreased in current years to ~70,000 [1,2] in children, there are at least 80 million cases of shigellosis each year worldwide, with the estimated disability-adjusted life years (DALYs) at 7 million and year loss due to disability (YLD) at 744,000 [1,2,3,4]. Shigella invades the mucosa, causing inflammatory destruction of the large intestinal epithelium, which can result in environmental enteropathy, chronic malnutrition, and cognitive and developmental impairment.

Shigella is known primarily as a cause of bacillary dysentery (blood/mucus in stool, which can be associated with fever and abdominal cramps). However, a large proportion (~40% to 89%) of Shigella-associated diarrhea cases are non-dysentery or secretory diarrhea in nature [5,6,7,8,9]. The clinical syndrome of dysentery caused by Shigella is readily identified clinically and warrants treatment with antibiotics, but Shigella infections causing watery diarrhea are not easily clinically recognized, and the clinical identification of these patients is difficult [7]. The current World Health Organization (WHO) guidelines for the treatment of diarrhea recommend antibiotics when there is the presence of visible blood in diarrhea stool [10,11]. Therefore, cases of non-dysentery Shigella-associated diarrhea (NDSD) are generally not treated with antibiotics.

Oral ciprofloxacin and azithromycin are considered first-line therapeutics for dysentery shigellosis (DS) in adults and children [12]. With effective antibiotic therapy for DS, clinical improvement occurs within 24 to 48 h, resulting in a decreased risk of serious complications and death, shortening the duration of symptoms, and reducing fecal carriage from ~4 weeks to 3 days, while also reducing transmission [12,13,14,15,16]. Thus, the current WHO guidelines appear to manage dysentery effectively but might miss opportunities to reduce mortality and long-term growth potential among children infected with Shigella who present with watery diarrhea.

It may be hypothesized that NDSD cases, if identified quickly, should be treated with antibiotics or other therapeutics to improve the survival and long-term developmental potential of the children. Shigellosis cannot be distinguished reliably from other causes of bloody diarrhea or other causes of watery diarrhea based on clinical features alone. Documenting NDSD infections and rationally guiding treatment will require a point-of-care (POC) test for Shigella so that the treatment can be initiated promptly. Chakraborty et al. previously developed and successfully evaluated, in Asian and African countries, a simple molecular diagnostic test for Shigella: the Rapid LAMP-based Diagnostic Test (RLDT), which detects Shigella from a fecal sample within one hour and thus has the potential to be used for the rapid detection and treatment of NDSD [17,18,19,20].

We are conducting a prospective longitudinal case–control study (INSIGHT) in Mirzapur, Tangail, Bangladesh, to determine if there is a need to change the current guidelines on shigellosis treatment for improving the survival and development of children with this condition. We will determine the impact of NDSD on immediate and long-term (1-year) morbidity and development in children under 5 years old compared with DS and non-Shigella watery diarrhea (WD). We will also assess the potential for implementation of the RLDT for Shigella in a rural primary healthcare government facility in Bangladesh.

## 2. Materials and Methods

### 2.1. Ethical Approval

The protocol for the INSIGHT study was developed through a collaborative effort among the researchers from Johns Hopkins University and the International Centre for Diarrhoeal Disease Research, Bangladesh (icddr,b). The INSIGHT study protocol was reviewed and approved by the Institutional Review Board of the Johns Hopkins Bloomberg School of Public Health and the Ethical Review Committee of the icddr,b. Written informed consent from the parents/caregivers will be obtained by study staff before any study procedures are carried out and confidentiality will be maintained throughout the study period. The results of this study will be submitted for publication in peer-reviewed journals.

INSIGHT is a prospective case–control study including 592 children under 5 years of age who are residents of Tangail seeking care in the Kumudini Hospital (KH) with NDSD, DS, or WD. Children will be given a certain standard of care by the hospital physicians as per the WHO and Bangladesh treatment guidelines. All children will be rehydrated with either intravenous therapy or ORS depending on the degree of their dehydration, and zinc will be provided. Children with DS will be treated with azithromycin or other antibiotics as recommended by the hospital’s attending physician.

### 2.2. Aims

The objectives of this study are to (1) determine the morbidity, risk of hospitalization, and mortality associated with NDSD cases; (2) study the impact of NDSD on the nutritional status and cognitive development of children; (3) understand the impact of NDSD on gut barrier function, systemic inflammation, and gut inflammation in children; (4) determine the Shigella isolates’ resistance to commonly used antibiotics using disk diffusion tests and E-strips; and (4) evaluate if the RLDT could be applicable for the detection and treatment of shigellosis cases in the low-resource clinical settings of a rural primary healthcare facility. The data from aims (1) to (3) will be compared between the NDSD group and the other two groups, DS and WD.

### 2.3. Study Setting and Population

The study children will be enrolled in the KH and followed through twice-weekly home visits. The KH is a nonprofit hospital located in the central urban union of Mirzapur, providing healthcare services to the surrounding poor rural population. Mirzapur is a rural sub-district (Upazila) of Bangladesh that covers 374 square km in the Tangail district. It is located 60 km northwest of the capital city, Dhaka.

### 2.4. Study Design

Children between 1 and 59 months with acute watery diarrhea, presenting to the KH, with a stool sample that is positive for Shigella according to the RLDT, will be enrolled in the study (named the NDSD group). For comparison, a second group of children with dysentery (presence of visible blood in stool) and positive for Shigella according to the RLDT (DS group) will be included (see enrolment flow chart in Figure 1). The DS group will be treated with antibiotics as a standard treatment. A third group of children with watery diarrhea negative for Shigella according to the RLDT (WD group) will also be enrolled. All RLDT-positive stool samples and 10% of the RLDT-negative stool samples selected at random will be confirmed for Shigella via culture analysis. All RLDT-positive stool samples will be re-tested by qPCR.

Following enrolment, the children in all three groups will be evaluated and compared based on the following factors to assess morbidity: whether requires hospitalization (inpatient), the severity of their diarrhea (the number of loose stools per day, the presence of sunken eyes, the loss of skin turgor, and whether intravenous hydration is required), other clinical symptoms (fever, rectal straining, abdominal pain and cramp, anorexia, convulsion, vomiting, etc.), the length of their illness, and their diarrheal severity score [21]. The duration of the shedding of Shigella bacteria in stool following the index diarrhea episode will be evaluated using stool samples collected on every other day until day 14 and then twice per week tested by the RLDT and culture until two consecutive stool samples are negative for Shigella by the RLDT.

During the follow-up period of 1 year for the NDSD and DS groups and 3 months for the WD group, the field workers will visit the households twice per week to collect morbidity data. Data on any episodes of diarrhea after the index diarrhea episode, including shigellosis (DS and NDSD), hospitalizations, and antibiotic use, will be collected during these visits. In addition to these data on future diarrhea episodes, stool samples will be collected every month and tested for Shigella using the RLDT and culture analysis. Parents or primary caregivers of the enrolled children will undergo standardized interviews to solicit demographic, socioeconomic, sanitation- and hygiene-related, epidemiological, and clinical information. Diarrhea will be defined as three or more loose or liquid stools during a 24 h period, and dysentery as one or more loose stools with visible blood. A diarrheal episode will be defined as “new” if the diarrhea definition is met after at least three or more days free of diarrhea or dysentery. Anthropometry (weight, length, mid-upper arm circumference, and head circumference) will be measured upon enrolment in the KH and every month during home visits by the field workers. The cognitive, language, and motor development of the children will be measured using the Bayley-IV for children 1 to 42 months of age and the Wechsler Preschool and Primary Scale of Intelligence (WPPSI-IV) and Ages and Stages Questionnaire for the older children [22]. The Ages and Stages Questionnaire (ASQ-3) is a developmental screening tool that will be used for measuring the motor development of the older children. Children’s behavior will be measured during the cognitive assessments through five Wolke scales based on their response to the assessor in the first 10 min, measuring their approach, emotional tone, cooperation with the assessor, vocalization, and activity level throughout the test. These ratings have been used previously on Bangladeshi children [23]. Home Observation for Measurement of the Environment (HOME) will be conducted once at the first visit after enrolment. Children’s behavioral assessments will be analyzed using Wolke’s Behavior Rating scale [24,25] by observing their behavior during the Bayley or WPPSI test. This assessment includes responsiveness to the examiner, activity level, emotional tone, cooperation with test procedure, and vocalization on a 9-point scale during the test. It has been proven that this scale is sensitive to intervention effects and can pick up group differences in Bangladeshi cohorts [24]. Two trained female assessors will administer the Bayley-IV, WPPSI, ASQi (motor component), and Behavior Rating tests in the field office through direct assessment, observations, and maternal interviews two days after the index diarrhea episode is resolved and at the 3- and 12-month follow-up visits. The assessors will receive a month-long extensive training on all of the developmental measures by the senior psychologist of the study and will be allowed to carry out data collection after achieving >85% inter-rater agreement with the trainer. To ensure data quality throughout the study period, the senior psychologist will conduct ongoing reliability checks of 10% of the total sample and ensure that refresher training is provided quarterly. Two female enumerators will collect the HOME data at the household level along with other demographic information.

For the detection of Shigella by culture analysis, stool samples will be cultured on MacConkey agar and Salmonella–Shigella agar followed by biochemical tests and then serotyped using commercially available antisera (Denka Seiken, Tokyo, Japan). The Shigella isolates will be tested for their susceptibility to ciprofloxacin, azithromycin, cefixime, ceftriaxone, trimethoprim/sulfamethoxazole, nalidixic acid, ampicillin, and pivmecillinam using the Kirby–Bauer disk diffusion method and the minimum inhibitory concentrations will be determined using E-strips. The isolates will be stored in glycerol stock.

### 2.5. Inclusion and Exclusion Criteria

The inclusion criteria are as follows: (1) children between >1 month and <60 months of age seeking care at the KH for diarrhea; and (2) children residing in the catchment area of the KH and willing to be available for sample and data collection during the scheduled visits. In addition, children in the NDSD and DS groups with stool samples positive for Shigella according to the RLDT will be included. The exclusion criteria are as follows: (1) children whose diarrhea episode started more than 72 h before enrolment; (2) children who have taken antibiotics within the last 3 days; (3) children with severe acute malnutrition (below the −3 Z score of the median WHO growth standards); and (4) children with another significant disease process requiring specific therapy. In addition, for the NDSD and WD groups, children showing the presence of visible blood in their stool will be excluded.

### 2.6. Collection, Preparation, and Archiving of Biological Samples

Stool and blood specimens will be collected at the baseline during enrolment at the hospital by the study staff and during follow-up home visits by the field staff following the schedule (Table 1) to evaluate inflammatory and immune markers. Gut barrier function will be assessed using the lactulose rhamnose (LR) permeability test, wherein urine will be collected before, 2 h after, and 5 h after the administration of LR solution to determine the ratio of L:R among the study children. Using blood serum, we will measure C-reactive protein, intestinal fatty-acid-binding protein, lipopolysaccharide, and flagellar (FliC) IgA and IgG levels to measure systemic inflammation, enterocyte death, and the translocation of pathogens. We will monitor gut inflammation by measuring the levels of myeloperoxidase (MPO) and lactoferrin (LF) in stool samples. The panel of 10 inflammatory cytokines (IL-2, -4, -6, -8, -10, -13, -1ß, TNF-α, IFN-γ, IL-17) will be tested in both serum and stool samples. Other major enteric pathogens will be detected in stool using quantitative PCR. All samples will be collected, processed, and stored following the standard operating procedures developed in the study protocol and following the schedule of events (Table 1).

In order to evaluate whether the RLDT could be implemented in a rural primary healthcare hospital in Bangladesh, we will train the hospital staff in the RLDT procedure and certify them. During the screening for enrolment in the INSIGHT study, 225 randomly selected stool samples will be sent to the rural hospital lab to be rescreened with the RLDT by the trained hospital staff, independently. The results will be compared with the RLDT results that were obtained by the INSIGHT study staff for the purpose of enrolling participants. We will determine the level of technical support needed for the RLDT, its ease of use, and its acceptability among the hospital lab staff using a questionnaire.

## 3. Statistical Considerations

### 3.1. Sample Size and Power

This study’s hypothesis is that the rates of hospitalization (inpatient) will be similar among the NDSD and DS cases. This is a matched set of cases (DS) and controls (NDSD) with two matched controls per case. The second comparison group is the WD group (1:1 matched with case). Based on previous data on the hospitalization rates of shigellosis cases in Mirzapur (obtained via personal communication with [name] et al.), we assume that the probability of hospitalization among the controls will be 20%. Since it is not known, as a general practice, the correlation coefficient for exposure between the matched cases and controls is set to 0.2. If the true odds ratio for hospitalization in the exposed subjects relative to the unexposed subjects is 0.5, we will need to study 123 cases of shigellosis with dysentery with 2 matched controls per case in order to be able to reject the null hypothesis that this odds ratio equals 1 with a probability (power) of 0.8. If the alternative hypothesis is not satisfied, then we will accept the null hypothesis of no difference in hospitalization rates between the cases and controls. The Type I error probability associated with the test of this null hypothesis is 0.05. With an estimated 20% of participants lost to follow-up, we will enroll 148 children each in the DS and WD groups and 296 in the NDSD group (total: 592).

For the RLDT evaluation in the primary healthcare facility, a sample size of 225 (45 subjects with Shigella) achieves 80% power to detect a change in sensitivity from 0.60 to 0.80 using a two-sided binomial test and 100% power to detect a change in specificity from 0.60 to 0.80 using a two-sided binomial test with the target significance level set to 0.05. The actual significance level achieved by the sensitivity test is 0.0336 and that achieved by the specificity test is 0.0397. The prevalence of the disease is ~20%.

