### 3.2. Statistical Analyses

The indicators of severity and symptoms determined by the morbidity indicators, hospitalization, and diarrheal disease score between the cases and controls at baseline (i.e., upon enrolment) will be evaluated using conditional logistic regression adjusting for sex and other confounding factors. The impact of the initial shigellosis or WD episode on the future morbidity, hospitalization, and mortality of the children, during the follow-up period of 12 months for the NDSD and DS groups or 3 months for the WD group, will be analyzed accounting for the confounding factors. Any antibiotic use during the follow-up period will be recorded and considered during analysis. Initially, bivariate conditional logistic regression models will be developed considering each one of the sociodemographic factors for the risk of shigellosis to select the variables for adjustment in the multivariable model.

The Z scores of all anthropometric measurements of the cases and their matched controls at different time intervals will be compared using paired *t*-tests. We will perform linear regression analyses comparing the baseline Z scores and changes in the Z scores from enrolment to the 3- or 12-month follow-up assessment, adjusting for the enrolment Z score, the duration of the follow-up period, sociodemographic covariates, antibiotic use, future diarrhea episodes, and any hospitalization in the follow-up period, using jack-knife estimates of standard error [26].

The same analytic techniques will be used for evaluating the data from the Bayley and WPPSI scales by comparing both the Z scores and age-adjusted composite scores of all developmental domains in the unadjusted model. In the multivariable-adjusted liner regression model, we will adjust specific baseline test scores for each domain and any other related sociodemographic variables that are significantly different between the groups at baseline, significantly different between the children lost to follow up and the tested children, or significantly associated with developmental outcome measures, e.g., socioeconomic status, sex, mother’s education, HOME assessment result, etc. Five behavioral outcomes will be summed up as total scores and will be used in a similar analysis. Sensitivity and mediation analyses will also be conducted using a Structural Equation Model (SEM) [27] to explore the underlying mechanisms or processes influencing the outcomes.

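### The matched analyses are built around the DS case, so as written none of them estimates the NDSD versus WD contrast that the aims promise

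*Protocol article*

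**What the plan says.** **Matching (section 3.1).** "This is a matched set of cases (DS) and controls (NDSD) with two matched controls per case". The next sentence brings in the third group: "The second comparison group is the WD group (1:1 matched with case". Enrolment is 148 DS, 296 NDSD and 148 WD, 592 in all. The hypothesis and the sample size calculation concern hospitalization in NDSD against DS only.

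**Promised comparisons.** Section 2.2: "The data from aims (1) to (3) will be compared between the NDSD group and the other two groups, DS and WD". The Introduction agrees: "We will determine the impact of NDSD on immediate and long-term (1-year) morbidity and development in children under 5 years old compared with DS", and the same sentence goes on to name WD. Section 2.4 is more general and names no pair: "the children in all three groups will be evaluated and compared".

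**Planned analyses (section 3.2).** The severity indicators, hospitalization and the diarrheal score "between the cases and controls at baseline (i.e., upon enrolment) will be evaluated using conditional logistic regression". For growth, "The Z scores of all anthropometric measurements of the cases and their matched controls at different time intervals will be compared", and the test named is the paired t-test. The Bayley and WPPSI data are to be handled with the same techniques. For the inflammatory markers, the comparison of magnitudes and kinetics names only DS and NDSD.

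**Follow-up (section 2.4).** One year for NDSD and DS, three months for WD.

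**The concern.** NDSD is the group the study is about. NDSD versus WD asks whether the presence of Shigella matters among children whose stool shows no blood, and so bears directly on the value of detecting these children. The matched analyses are written around a different index group. If an analyst applies the section 3.1 definitions to section 3.2, the WD children are set against DS.

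DS versus WD cannot stand in for NDSD versus WD. By the article's own description, DS and WD children differ in three respects at once: Shigella status, visible blood, and planned antibiotic treatment. At stake is whether the analysis that uses the matching answers aims 1 to 3, or whether NDSD versus WD falls to an unmatched comparison that someone has to devise after the data are in.

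**Working it through.** **Step 1: which group is the anchor?** The wording of section 3.1 says DS, and the group sizes allow a check.
- Anchor DS: 148 DS, 2 × 148 = 296 NDSD, 1 × 148 = 148 WD. Total 148 + 296 + 148 = 592, which is the stated total.
- Anchor NDSD, with WD matched 1:1 to it: 296 WD would be needed. Total 148 + 296 + 296 = 740, which is not the stated total.

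The sizes fit only DS as the anchor. (The figure 148 is 123 × 1.2 = 147.6, rounded up. Whether 123 follows from its own inputs is a separate matter, and this point does not depend on it.)

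**Step 2: set the promises beside the matched analyses.** Case = DS; matched controls = NDSD (2) and WD (1).

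| Contrast | Promised for aims 1 to 3 (2.2) | Given by the matched analyses of 3.2 under the 3.1 definitions |
|---|---|---|
| NDSD v DS | yes | yes |
| NDSD v WD | yes | no |
| DS v WD | no | yes |

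**Step 3: does the paired t-test fit the sets?** It needs one difference per pair. A set with one DS and two NDSD children gives two differences, DS − NDSD₁ and DS − NDSD₂, which share the DS child. Over 148 sets that is 2 × 148 = 296 differences that are not independent. The plan would have to average the two NDSD values or model the set, and it states neither. NDSD versus WD has the same problem, because the set's one WD child faces two NDSD children.

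**Step 4: can DS versus WD substitute?** In one logistic model, OR(DS:WD) = OR(DS:NDSD) × OR(NDSD:WD). Under the odds ratio of 0.5 assumed in section 3.1, the first factor is 0.5, so the two WD contrasts differ by a factor of 2 whatever the WD risk is. They coincide only if OR(DS:NDSD) = 1, and that is what the study sets out to examine.

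**Step 5: can NDSD versus WD be recovered from the design as enrolled?** Yes. Take the set (1 DS + 2 NDSD + 1 WD) as the stratum, with indicators for DS and WD and NDSD as reference. One conditional logistic model then gives both promised contrasts: exp(β_DS) for DS versus NDSD and exp(β_WD) for WD versus NDSD. The same two indicators with a set effect serve for continuous outcomes.

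**The case against.** The strongest reply has four parts.

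- **The word *case* is used loosely.** The article also speaks of NDSD cases, and section 3.2 plans models for the risk of shigellosis, which need WD as the comparator and would naturally place NDSD on the Shigella side. This stands as a point about ambiguity. A reader might infer that the authors firmly chose DS versus WD in place of NDSD versus WD, and the text does not show that. But the one explicit definition is in section 3.1, and the group sizes follow it.
- **Other analyses can carry the contrast.** Section 3.2 has an adjusted follow-up analysis that names all three groups, and linear regressions of change to 3 or 12 months, where 3 months is the end of WD follow-up. Section 2.4 and the Discussion put all three groups side by side. This stands too: it would be wrong to infer that WD enters only to be compared with NDSD, or that NDSD and WD are never compared. As written, though, these regressions are not matched, and the three-group statements name neither a pair nor a method.
- **The children share a set, so nothing is lost.** True, and the fix rests on it. It also rules out the inference that WD must be re-matched or more children enrolled. But section 3.1 describes a set only for DS and NDSD, and no stated analysis uses the joint set.
- **Such detail belongs in the analysis plan.** That would answer a mere omission. Here the article fixes a case/control rule and a paired test that do not deliver a contrast promised by its own aims.

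**Conclusion.** The point holds as a mismatch between the aims and the stated matched analyses, not as a fault in enrolment. Of the two contrasts promised for aims 1 to 3, NDSD versus DS has a stated matched analysis and NDSD versus WD (296 against 148 children) has none. The paired t-test does not suit the 2:1 part of the set for either contrast.

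This rests on reading *case* as section 3.1 defines it, which the 148:296:148 split supports, and on DS, NDSD and WD children matched to the same DS child being treated as one set.

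Two further inferences should be resisted. The documents give no hospitalization rate for WD, so the direction and size of any error in the WD results cannot be stated. And the sample size in section 3.1 concerns NDSD versus DS alone, so no power should be claimed for NDSD versus WD.

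**What to change.** Keep enrolment and matching as they are.

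1. In section 3.1, define the matched set as 1 DS + 2 NDSD + 1 WD, and state that the sample size was set for NDSD versus DS only.
2. In section 3.2, name NDSD as the reference group and replace the case/control wording with two contrasts: NDSD versus DS, and NDSD versus WD.
3. For binary outcomes, use conditional logistic regression stratified on set. For growth and development, replace the paired t-tests with a model that includes a set effect.
4. Limit the WD contrasts to outcomes up to 3 months, the end of WD follow-up.

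The cost is a few sentences in 3.1 and 3.2 and a set identifier carried in the data. No extra children, visits or tests are needed. The change should be fixed before outcome data are analysed.

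### 123 matched sets do not give 80% power for the stated inputs; the matched formula needs about 224 and gives about 52% power at 123

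*Protocol article*

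**What the plan says.** Section 3.1 (Sample Size and Power) of the protocol article gives one power calculation for the main hypothesis, which is that hospitalization is similar in non-dysentery Shigella diarrhea (NDSD) and Shigella dysentery (DS).

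- Design: "This is a matched set of cases (DS) and controls (NDSD) with two matched controls per case".
- Control rate: "we assume that the probability of hospitalization among the controls will be 20"%.
- Correlation: "the correlation coefficient for exposure between the matched cases and controls is set to 0.2".
- Effect: "If the true odds ratio for hospitalization in the exposed subjects relative to the unexposed subjects is 0.5".
- Error rate: "The Type I error probability associated with the test of this null hypothesis is 0.05".
- Result: "we will need to study 123 cases of shigellosis with dysentery with 2 matched controls per case", in order to "reject the null hypothesis that this odds ratio equals 1 with a probability (power) of 0.8".

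If the alternative is not met, the plan will "accept the null hypothesis of no difference in hospitalization rates between the cases and controls". The 123 is then raised to 148 DS and 296 NDSD children to allow for an estimated 20% loss. Section 3.2 names conditional logistic regression for hospitalization at baseline.

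**The concern.** The paragraph prints a full set of inputs and a result, so the result can be checked. An odds ratio of 0.5 against 20% is a difference of roughly 11% versus 20%. That is a modest absolute difference for 123 cases and 246 controls, and even an unmatched comparison of those proportions needs far more than 123 cases.

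The decision rule raises the stakes. The study expects similarity and will accept the null when the test is not significant. The Type II error is therefore the chance of wrongly supporting the study's own hypothesis when the odds in fact differ twofold. The reader is told that this chance is 20%. No other power statement covers the main hypothesis, and the total of 592 children is built on the 123.

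**Working it through.** **Inputs (all section 3.1).** Control probability p0 = 0.20; odds ratio ψ = 0.5; correlation φ = 0.2; M = 2 controls per case; α = 0.05; power 0.80. Sidedness is not given for this test. I take it as two-sided because the null is an odds ratio of 1 with no direction.

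**Case probability.** p1 = p0ψ / (1 − p0 + p0ψ) = 0.10 / 0.90 = 0.111.

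**Dupont formula.**

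1. Probability that a control is hospitalized, given the case's status. With s = φ√(p1q1p0q0):
   - case hospitalized: (p1p0 + s)/p1 = 0.426
   - case not hospitalized: (p0q1 − s)/q1 = 0.172
2. Probability that a set holds m hospitalized children: t1 = 0.2894, t2 = 0.0806.
3. Moments, summing over m = 1, 2:
   - e(ψ) = Σ m·t_m·ψ / (mψ + M − m + 1), so e(1) = 0.1502 and e(0.5) = 0.0982
   - v(ψ) = Σ m·t_m·ψ·(M − m + 1) / (mψ + M − m + 1)², so v(1) = 0.0822 and v(0.5) = 0.0664
4. n = [0.842·√0.0664 + 1.960·√0.0822]² / (0.1502 − 0.0982)² = 0.607 / 0.00271 = **224.2 sets** (unrounded values carried).
5. Power at n sets = Φ{[√n·0.0520 − 1.960·√0.0822] / √0.0664}. This gives **52% at 123** and **61% at 148**.

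**Cross-checks, two-sided, 20% in controls and odds ratio 0.5:**

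| Calculation | Sets for 80% | Power at 123 |
|---|---|---|
| Dupont, φ = 0.2, p1 = 0.111 | 224.2 | 52% |
| Dupont, φ = 0.2, p1 = 0.126 (conditional OR exactly 0.5) | 219.8 | 53% |
| Dupont, φ = 0 | 197.8 | 58% |
| Unmatched 1:2, 11.1% vs 20% | 201 | 58% |
| Marginal difference test, correlation reduces variance, pooled | 160.8 | 68% |
| Same, unpooled variance | 143.5 | 74% |

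**Simulation of the 1:2 conditional score test** (40,000 replicates, two-sided):

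| Reading | 123 sets | 148 sets |
|---|---|---|
| Conditional OR 0.5, φ = 0.2 | 48% | 57% |
| OR 0.5, φ = 0 | 59% | 67% |
| Marginal OR 0.5, φ = 0.2 | 67% | 76% |

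The last row is higher because a marginal odds ratio of 0.5 with correlation 0.2 implies a stronger matched odds ratio. The ratio of discordant probabilities is (0.111 × 0.574) / (0.889 × 0.172) = 0.42.

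**Where a figure near 123 does appear.** Each route changes an input or the method:

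- Dupont, OR 2.0, φ = 0: 125
- Dupont, OR 0.40, φ = 0: 124
- Dupont, conditional OR 2.0, φ = 0.2, one-sided: 122
- Marginal test, OR 0.5, φ = 0.2, one-sided: 126 (79% power at 123)
- Unmatched, risk ratio 0.5, one-sided: 121

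**What 148 sets can detect** (Dupont, φ = 0.2, two-sided): OR 0.41, i.e. 9.3% vs 20%, with power 81%; OR 2.0, i.e. 33% vs 20%, with power 79.5% (150.1 sets for 80%).

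**The case against.** Four points can be made for the plan.

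- **Sidedness.** The paragraph does not say that this test is two-sided, and a one-sided marginal test comes to 126. So two-sided is an assumption, and 123 cannot be called impossible under every method. But the null has no direction, the planned analysis is conditional, and the one-sided matched formula still needs 175 sets.
- **Direction.** The text speaks of exposed and unexposed subjects without saying which group is which. If a doubling of the odds in DS was meant, the formula needs 150 sets at the stated correlation. The 148 enrolled would then be nearly enough, and the fault would lie mostly in the description. A marginal test on that reading would need only about 101. This is a real possibility, but the printed value is 0.5, and the matched formula at OR 2.0 still gives only 72% at 123.
- **Method.** The required number depends on method, from 144 (unpooled marginal variance) to about 224. No single corrected figure is beyond dispute. All of them exceed 123.
- **Enrolment margin.** Hospitalization is compared at enrolment, so later loss need not reduce the number of sets, and 148 may be the fair figure. On that basis power is 57% to 76% by simulation; at the top of that range the shortfall is small.

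**Conclusion.** The concern holds. With the inputs printed in section 3.1 and a two-sided 0.05 test, 123 matched sets do not give 80% power under any calculation tried. By the formula that takes those inputs, the chance of missing a halving of the odds is about 48% at 123 sets and 39% at 148, against the 20% implied. By simulation it is 33% to 52% at 123 and 24% to 43% at 148. The conclusion rests on a two-sided test, the odds ratio of 0.5 as printed, and the matched analysis named in section 3.2. The exact size of the shortfall depends on whether the odds ratio is read as conditional or marginal; its existence does not. Because a non-significant result will be taken as no difference, the power statement has to be corrected.

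**What to change.** Keep the enrolment and replace the power statement. Suggested text, if the odds ratio of 0.5 is DS relative to NDSD:

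> With 148 matched sets (one DS case, two NDSD controls), 20% hospitalized among NDSD children, a within-set correlation of 0.2 and a two-sided Type I error of 0.05, power by the Dupont formula is about 61% for an odds ratio of 0.5. Power of about 80% is available for odds ratios (DS relative to NDSD) of about 0.41 or about 2.0.

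The authors should also state which group is the reference, whether the odds ratio is conditional or marginal, whether the test is one- or two-sided, and the software and inputs that produced 123. If an odds ratio of 2.0 or a one-sided test was intended, say so and recompute.

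The cost is a rewritten paragraph and a less favourable stated power. No extra children are needed.
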